### Proteomics analysis

3.4

For proteomics analysis samples stored at −80°C will be thawed and kept on ice before sample preparation. Disulfide bonds of proteins will be reduced using dithiothreitol , and free thiol alkylated with iodoacetamide. Proteins will be digested using trypsin as digesting enzyme. To enhance protein purification, denaturation, and digestion, the above-mentioned passages will be done in S-trap column (PROTIFI, New York, USA). After digestion, peptides will be eluted from the S-trap column, and they will be derivatized with tandem mass tag reagents (TMT kit Thermo Fisher, Milan, Italy). Samples will be further purified, combined for multiplexing analysis, and concentrated. Liquid chromatography–high resolution mass spectrometry analysis will be performed at the Unitech OMICS of the University of Milan, using a Dionex UltiMate3000 nanoflow liquid chromatography (nanoLC) connected in-line with an Orbitrap Fusion mass spectrometer (Thermo Scientific, Milan, Italy).

Data analysis for protein identification and quantification will be carried out with Max Quant software and further filtered with Perseus (Max Plank Institute of Biochemistry, Germany). Networks and pathways analysis will be done with STRING (Swiss Institute of Bioinformatics) and Ingenuity Pathways Analysis (QIAGEN, Hilden, Germany) software.

### Statistical analysis

3.5

Descriptive statistics of continuous variables understudy will be presented as mean ± SD; categorical variables were expressed as absolute numbers and percentages. The differences in continuous variables will be assessed using the Mann–Whitney *U* test when not normally distributed, and the Student *t* test when normally distributed. The *X*^2^ test was used to test for differences in categorical variables. The relationship between all variables before and after active/placebo treatment will be tested by Spearman correlation coefficients and their 95% confidence intervals.

The primary outcome variable is the treatment-related change in any of the Sal parameter understudy, before and after active/placebo treatment in Cs/Ds subjects by intention to treat criteria, that is, including all patients with adequate sampling before and after treatment (7 days). Differences in treatment-related changes between the groups will be analyzed in the context of covariance analyses (ANCOVA), which included terms for treatment and baseline values as covariates. Treatment effects were assessed by the least-squares mean change from the above ANCOVA model.

If relevant, the intra- and inter-observer variability of sampling, as well as measurements, a repetition of sampling and data analysis will be performed. For intra-observer variability the primary observer will sample/analyze the data on 2 different days; for inter-observer variability the sample/analysis will be performed, independently, by a second observer who was blinded to previous results. Intra- and inter-observer variability will be calculated as the coefficient of variance, which is the standard deviation of the difference between observations divided by their mean and multiplied by 100.

The size of the sample and the power will be calculated expecting a type I error rate of 5% or less. When appropriate, a value of *P* < .05 will be considered significant.

If samples are missing for any cause (eg, not compliance with the trial protocol, no follow-up, others) they will be removed from the analysis.

Data will be analyzed at the end of the study when all samples will be collected. Access to the data in anonymized mode will be provided to the investigators.

A computer statistical package will be used to validate the model and to perform the analysis (SPSS v.20, IBM, Armonk, New York, USA).

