### Subjects selection

3.1

Among subjects referring to the OUC, we will enroll, on a voluntary basis, n = 40 diseased subjects (Ds), aged 18–40 years having at least 1 of the following OD: (a) dental erosions, (b) caries, and (c) périodontopathies, for example, gingivitis or aggressive/chronic periodontitis.

The criteria for each OD were defined on the basis of commonly accepted grading scores in dentistry. Dental erosions will be counted; for caries, we will adopt the missing and filled dental criteria; for périodontopathies, we will record the probing depth, clinical attachment loss, plaque index, and bleeding on probing using a manual periodontal probe.

A complete medical and dental history will be obtained from all participants; all the volunteers must not present allergies/intolerances to the consumption of Car or take other food supplements or any type of drug treatment (interview). Exclusion criteria will be also smoking, pregnancy/lactation, and the presence of any systemic diseases such as cardiovascular and respiratory, diabetes mellitus, HIV infection, or inflammatory conditions causing non-plaque dependent OD. Patients eligible for the study will return to the OUC after being pre-screened. Before being enrolled in the study, participants will provide written and informed consent for use of their saliva samples and clinical data for scientific research purposes. The study is in accordance with the guidelines of the World Medical Association Declaration of Helsinki.

A control group (Cs) of 20 age-matched subject with periodontal health will be enrolled among the staff of the OUC. The number of subjects identified and considered sufficient for the research is based on a preliminary test conducted on the salivary flow obtained from the staff involved in the project. The schedule of enrolment, interventions, and assessments, and the flow-chart of the protocol are depicted in Figures 1 and 2.

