### Administration of Car

3.3

Subjects understudy will be instructed to assume Salifluss^TM^ twice a day, in the morning and before bedtime. Salifluss^TM^ is a Class I medical device according to EU Dir. no 93/42/CE (as amended by EU Dir. No. 2007/47/CE), notified to Italian Ministry of Health with ID number 1810197/1810202. At recommended doses, the intake quantities of the substances meet the requirements and limitations set by the Italian Ministry of Health. As previously introduced, Salifluss^TM^ is a 400 mg mucoadhesive oral tablet (13 × 4 mm^2^) with smooth surfaces whose main ingredient is Car. The tablet should be placed in the gingival fornix and, thanks to its mucoadhesiveness, let to dissolve slowly. The dissolution time of the tablet is around 2 hours in normal salivation conditions. Placebo tablets, similar to Salifluss^TM^ ones, will be administered to randomly selected n = 20 subjects, 10/10 from Cs/Ds. An SMS reminder will be sent to all the subject reminding to take the pill.

Patients will be encouraged to report any adverse events and other unintended effects of trial interventions.

Attached the technical and safety data sheets, the certificate of analysis, and the sell-sheet of the extract of Cr.

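### Healthy v diseased comparison (20 v 40) rests on Student t or Mann–Whitney, chosen by normality alone, with no provision for unequal spread

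*Protocol article*

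**What the plan says.** In the protocol article, Statistical analysis gives a general rule for differences in continuous variables: the Mann–Whitney test "when not normally distributed, and the Student *t* test when normally distributed". No unequal-variance form is named. The decision threshold is "When appropriate, a value of *P* < .05 will be considered significant".

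Treatment-related change, the primary outcome, is handled separately by an ANCOVA with treatment and baseline terms.

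The group sizes are fixed elsewhere. Subjects selection enrols 40 diseased subjects (Ds) who have at least one of erosions, caries or periodontal disease, and "A control group (Cs) of 20 age-matched subject with periodontal health", drawn from clinic staff. Administration of Car gives placebo to "randomly selected n = 20 subjects, 10/10 from Cs/Ds". By subtraction, 30 Ds and 10 Cs receive active tablets.

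Aim of the study and Discussion both make the comparison of saliva characteristics with oral disease a purpose of the trial.

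**The concern.** Student t pools the two variances. Pooling does little harm when the groups are equal in size or in spread. With unequal sizes, the pooled estimate is dominated by the larger group, so the standard error is wrong whenever the spreads differ.

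The Cs v Ds comparison is exposed to this. It is 20 v 40 and not randomised. One group is selected for periodontal health and the other mixes several conditions. Age-matching does not equalise the spread of flow, pH or protein abundance. A normality check does not detect the problem, because two normal samples can have quite different variances. Mann–Whitney is also affected by unequal spread.

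What is at stake depends on which group is more variable. If it is Ds, real differences between healthy and diseased saliva are more easily missed. If it is Cs, differences are declared too often.

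**Working it through.** **Inputs from the article:** n = 20 (Cs) and n = 40 (Ds), from Subjects selection; threshold P < .05, from Statistical analysis.

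**Assumptions:** two-sided testing, normal data and equal means under the null. The article gives no SDs, so SD ratios of 1.5 and 2 in each direction are illustrative.

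**Formulas.** With SDs σ₁ (Cs) and σ₂ (Ds):
- Squared standard error that Student t uses, on average: [(19σ₁² + 39σ₂²)/58] × (1/20 + 1/40)
- True squared standard error: σ₁²/20 + σ₂²/40
- k = square root of (Student / true)
- Approximate size = 2[1 − Φ(1.96k)]

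**Equal SDs (σ₁ = σ₂ = 1).** Both expressions equal 0.075, so k = 1 and the nominal 5% is reproduced.

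**Ds more variable (σ₂ = 1).**
- 1.5 times (σ₁ = 0.667): Student 0.8180 × 0.075 = 0.0614; true 0.0222 + 0.0250 = 0.0472; k = 1.140; size about 2.6%.
- 2 times (σ₁ = 0.5): Student 0.7543 × 0.075 = 0.0566; true 0.0125 + 0.0250 = 0.0375; k = 1.228; size about 1.6%.

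**Cs more variable (σ₂ = 1).**
- 1.5 times (σ₁ = 1.5): Student 1.4095 × 0.075 = 0.1057; true 0.1125 + 0.0250 = 0.1375; k = 0.877; size about 8.6%.
- 2 times (σ₁ = 2): Student 1.9828 × 0.075 = 0.1487; true 0.2000 + 0.0250 = 0.2250; k = 0.813; size about 11.1%.

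**Simulation, 20 v 40.** There were 40,000 runs per cell (8,000 for the two-step rule). The article names no normality test, so the two-step column assumes Shapiro–Wilk at 0.05 in each group.

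| SD ratio Cs/Ds | Student t | Mann–Whitney | Two-step | Welch |
|---|---|---|---|---|
| 0.5 | 1.8% | 3.2% | 1.9% | 4.9% |
| 0.67 | 2.6% | 3.7% | 2.8% | 4.9% |
| 1 | 5.0% | 4.9% | 5.0% | 5.0% |
| 1.5 | 8.5% | 6.7% | 8.4% | 5.0% |
| 2 | 11.1% | 8.5% | 11.5% | 5.0% |

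With normal data, the two-step rule behaves almost like Student t, because the check usually passes.

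**Power in the conservative direction.** Take a true difference of 1.96 + 0.84 = 2.80 true standard errors, which gives Welch about 80%. Student's power is then about Φ(2.80 − 1.96k):
- Ds 1.5 times: Φ(2.80 − 2.23) = Φ(0.57), about 72%.
- Ds 2 times: Φ(2.80 − 2.41) = Φ(0.39), about 65%.

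Simulation gives the same figures.

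**Other contrasts.**
- Active v placebo within Cs is 10 v 10, and Student t stays at 5.1% to 6.0% for SD ratios from 1/3 to 3.
- Active v placebo within Ds is 10 v 30, and pooled it is 20 v 40. Treatment-related change in these goes to the ANCOVA.
- An ANCOVA with one common residual variance has the same sensitivity. With residual SD ratios (smaller/larger group) of 0.5, 1.5 and 2, its size is 1.8%, 8.5% and 10.6% at 20 v 40, and 1.1%, 10.4% and 15.4% at 10 v 30.

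**The case against.** A reader might infer that the 5% level fails whenever the spreads differ. The documents do not support that. The level is exceeded only if the smaller group is the more variable. The one reason the article offers for unequal spread, the mixture of conditions in Ds, points the other way, to a conservative test that costs power. No SDs are given, so neither direction can be established.

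A reader might also take "expecting a type I error rate of 5% or less" as a guarantee for every comparison that the rule then breaks. That phrase belongs to the sentence on calculating sample size and power. The threshold for significance is stated separately.

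The 10 v 30 contrast tempts a stronger claim, because its figures are larger. However, treatment-related change is assigned to the ANCOVA, not to the t test. Placebo is randomly assigned, so if treatment has no effect in any subject the two arms have the same distribution and 5% holds. Inflation there needs equal means together with a wider placebo arm, for which the article gives no reason.

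Finally, a condensed article may leave the variance form to the analysis plan, which is not shown, and the planned software may report both forms. This limits the severity. It does not remove the point, because the article names Student t and makes normality the only criterion for leaving it.

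What stands is the non-randomised Cs v Ds comparison, where nothing protects the equal-variance assumption.

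**Conclusion.** The point holds in a conditional form. For Cs v Ds at 20 v 40, the named tests are reliable only if the two spreads are similar, and the design gives no ground for assuming so. At assumed SD ratios of 1.5 to 2, Student t either loses about 8 to 15 points of power (80 − 72 and 80 − 65) if Ds is the more variable, or has a true size of about 8.5% to 11% if Cs is. Mann–Whitney is only a partial remedy. Under these assumptions Welch is close to 5% in both directions.

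The primary treatment comparison is touched only through the ANCOVA's common-variance assumption, and much less there because allocation is random. Severity is minor to moderate. Confidence is moderate, because the SD ratios are not in the documents.

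**What to change.** Replace the general rule with a sentence to this effect: *Between-group differences in continuous variables outside the ANCOVA, in particular healthy v diseased, are tested with Welch's unequal-variance t test. No preliminary normality test is used to select the test, and any transformation is chosen in advance for each variable.* The article gives no basis for imposing a log scale on particular variables, so that choice stays with the sponsor, provided it is fixed before the data are seen.

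Optionally, report heteroscedasticity-robust standard errors as a check on the unbalanced ANCOVA.

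The cost is one sentence, and the Discussion says the study has not started. If variances are equal, Welch gives up under 1 point of power at 20 v 40, and about 3 points if it is also used for a 10 v 30 comparison.

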## Introduction

1

The pH of the oral cavity (OC) is a synthetic parameter that underlies a multifactorial process of continuous adjustment including the effect of saliva^[1]^ as a buffer and the contribution of the OC microbiome.^[2]^ In some diseases of the OC an impairment of these adjustment mechanisms is supposed to alter the normal flow of saliva and, consequently, the pH and the oral microbiome (OM)^[3]^ with the expansion of potentially pathogenic strains such as the most cited streptococcus viridans.^[4]^

Carnosine (Car) is an endogenous dipeptide, composed of β-alanine and l-histidine, that was originally discovered in larger amounts in skeletal muscle of some vertebrates, including humans, showing a greater dependence on non-oxidative forms of energy metabolism.^[5]^ This peculiar association with muscular tissue and its pH-buffering properties has led to associate Car with the intracellular acid-base homeostasis of muscles.^[6]^ More recently, the physiological role of Car has been expanded beyond the intracellular buffering properties, supporting a role in sarcoplasmic Ca^2+^ regulation and neutralization of reactive oxygen species (ROS). It is well known that ROS induce the formation of reactive electrophilic carbonyl species by reacting with lipids and sugars which, in turn, react with proteins forming irreversible adducts (AGEs, ALEs, and EAGLEs) and cross-links that may affect the cardiovascular wall matrix that becomes less distensible, especially during the aging process and/or diseases.^[7]^ Thus, it is thought that Car and, indeed, other histidine-containing peptides, may prevent chronic diseases via their anti-inflammatory, anti-oxidative, anti-glycating, anti-ischaemic, and chelating properties.^[8]^ Furthermore, the localization of Car in other tissues such as the brain, olfactory bulb, heart, stomach, pancreas, kidney has suggested further potential uses in preventing, for example, neurodegenerative disorder and cognitive function or the development of type II diabetes.

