## Aim of the study

2

The main objectives of this protocol are to estimate the quantity/quality of oral salivae and OM in healthy volunteers and in subjects affected by common OD, before and after 7 days of treatment with Salifluss^TM^, 1 tablet twice a day. The characteristics of oral saliva (Sal) that will be studied are (a) unstimulated and stimulated (paraffin-activated) salivary flow rates and pH and (b) quantitative proteomics (QP), on selected targets, representing the main proteins/components of OM.

By matching Sal characteristics with OM and comparing them with OD, we do expect to elucidate their mutual relationship; furthermore, using specific bioinformatics tools to analyze the data, before and after treatment with Car, we are looking to see its potentials on preventing/treating OD and, using QP, eventually elucidate the mechanism of action.

The study will take place at the Odontoiatric University Clinic (OUC), Istituto Stomatologico Italiano (ISI) of Milan, Italy, in a prospective, randomized, double-blind, and placebo-controlled fashion.

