### Sampling

3.2

Since the study is focused on saliva samples, subjects with severe hypo-salivation at the first sampling (saliva flow rate at baseline <0.1 mL min^−1^), because of their inability to dissolve the tablet formulation, will be rolled out. Saliva production will be determined by the spit method at baseline (*t* = 0) and after 7 days of treatment (*t* = 1) with Salifluss^TM^ twice a day or placebo.

The participants will be asked to avoid oral hygiene practices including flossing, brushing, and mouth-rinses as well as eating, and drinking for at least 2 hours before collection. Before sampling, the mouth will be rinsed with water for 2 minutes, and the subject will be asked to wait for 10 minutes.

The saliva samples will be obtained in the morning (8.00 am–10.00 am) according to the circadian rhythms in salivary flow.^[11]^ The unstimulated saliva samples will be collected by expectorating into sterile 50 mL tubes every 30 seconds. for 5 minutes as described earlier.^[12]^ The stimulated saliva will be collected in the same way after 2 minutes of chewing a paraffin wax ball.

The samples collected by an operator unaware of clinical data will be weighted, the pH will be measured by a pH-sensitive electrode, then centrifuged at 5000 *g* for 10 min at 4°C; the obtained supernatants will be supplemented with EDTA-free Protease Inhibitor Mixture (Sigma–Aldrich, Dorset, UK) and stored al −80° for the QP analysis. The collected samples will be analyzed at the Department of Pharmaceutical Sciences “Pietro Pratesi,” University of Milan, Milan, Italy (DISFARM) research laboratory.

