## Discussion

4

From this study, we do expect to elucidate the mutual relationship between Sal characteristics and OM and to compare them with OD; furthermore, using specific bioinformatics tools to analyze the data, before and after treatment with Car, we are looking to see its potentials on preventing/treating OD and, using QP, eventually elucidate the mechanism of Car supplementation.

The study is not yet started, no related publications containing the results of this study have already been published or submitted to any journal; the results of the trial will be shared only by scientific publication.

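### The plain Spearman correlations have no term for disease group, so a coefficient pooled over diseased and healthy subjects can show a saliva-microbiome link that exists in neither group

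*Protocol article*

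**What the plan says.** The protocol article's Statistical analysis section gives one sentence on association: "The relationship between all variables before and after active/placebo treatment will be tested by Spearman correlation coefficients and their 95% confidence intervals". It mentions time and treatment but not disease group. The same section does mention Cs/Ds when it defines the primary outcome, and it lists the ANCOVA terms (treatment and baseline value). The correlation sentence has no such list.

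These correlations serve a stated aim. The Aim of the study section says "By matching Sal characteristics with OM and comparing them with OD, we do expect to elucidate their mutual relationship", and the Discussion repeats it: "we do expect to elucidate the mutual relationship between Sal characteristics and OM and to compare them with OD".

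The sample is fixed by design. Subjects selection calls for "n = 40 diseased subjects (Ds), aged 18–40 years having at least 1 of the following OD" and adds "A control group (Cs) of 20 age-matched subject with periodontal health will be enrolled among the staff of the OUC". In Administration of Car, placebo "will be administered to randomly selected n = 20 subjects, 10/10 from Cs/Ds". The Introduction states the expected direction: "In some diseases of the OC an impairment of these adjustment mechanisms is supposed to alter the normal flow of saliva", with pH and the oral microbiome changing as a consequence.

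**The concern.** The two groups are chosen because they differ in oral health, and the protocol's own hypothesis is that this goes with differences in both saliva and microbiome. Where two groups differ on both variables, a rank correlation across the combined sample is pulled away from zero even if the variables are unrelated inside each group. Such a coefficient would only restate that diseased and healthy subjects differ. It would not show that saliva and microbiome vary together from one subject to the next, which is how a reader would take a mutual relationship.

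The effect is on the estimate itself. A stricter significance threshold would make such findings rarer but would leave the coefficient where it is.

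**Working it through.** The protocol gives no expected correlation, group gap or SD, so there is no figure of its own to reproduce. The check asks what a pooled coefficient shows when the true within-group correlation is zero.

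**Inputs from the protocol**
- Ds = 40 and Cs = 20 (Subjects selection), so the Ds share is p = 40/60 = 2/3.
- Placebo: 10 Cs and 10 Ds (Administration of Car). Active, by subtraction: 20 − 10 = 10 Cs and 40 − 10 = 30 Ds.

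**Assumption**
- The Cs/Ds gap is d SD on both variables, with d from 0 to 2.

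**Formula** (Pearson scale, zero correlation within groups)

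r = p(1 − p)d² / [1 + p(1 − p)d²]

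For the full sample, p(1 − p) = (2/3)(1/3) = 2/9. For example, at d = 1, r = 0.222/1.222 = 0.18; at d = 1.5, r = 0.5/1.5 = 0.33.

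**Simulation** (10,000 runs per row; one time point, 60 subjects; Spearman rho with a Fisher-z 95% interval, SE = √[(1 + r²/2)/(n − 3)])

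| Gap d (SD) | Formula r | Mean pooled rho | Interval excludes 0 | Same, ranks centred within group |
|---|---|---|---|---|
| 0 | 0.00 | 0.00 | 4.7% | 4.8% |
| 0.5 | 0.05 | 0.05 | 6.0% | 4.1% |
| 0.8 | 0.12 | 0.12 | 15.0% | 4.7% |
| 1.0 | 0.18 | 0.18 | 26.1% | 4.3% |
| 1.5 | 0.33 | 0.34 | 76.6% | 4.7% |
| 2.0 | 0.47 | 0.47 | 98.5% | 5.4% |

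The last column adjusts for group by centring the ranks within Cs and within Ds. Mean rho is then about 0.00 at every gap.

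**Does splitting by arm or time point remove the problem?** No, because each arm still holds both groups. At d = 1:
- Placebo (10 Cs, 10 Ds): p(1 − p) = 0.25, so r = 0.25/1.25 = 0.20.
- Active (10 Cs, 30 Ds): p(1 − p) = 0.1875, so r = 0.1875/1.1875 = 0.16.

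The arms would show slightly different correlations through case mix alone. This also shows how the value depends on the mix: 0.20 at 1:1, 0.18 at 2:1 and 0.16 at 3:1, all for the same underlying gap. The gap itself matters far more than the mix.

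**The case against.** Five points can be made on the other side.

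1. **The article does not say that Cs and Ds are pooled, and a fuller plan may settle it.** This is fair, and it limits the weight of the point. But the article does state the method, the variables and the interval, and the method as stated does not isolate the relationship that the aim names. Recommending group-specific or group-adjusted coefficients is a choice of method, not a request for more wording.

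2. **Disease may be downstream of saliva and microbiome.** On the protocol's own account, altered saliva disrupts the microbiome and disease may follow. Adjusting for a consequence does not remove confounding and can distort the association, and the between-group contrast is partly of interest. This stands as a reason not to discard the pooled value and not to call the adjusted one causal. It does not rescue the pooled value as the only result: subjects are selected on disease status, so that value depends on the 2:1 sampling ratio.

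3. **The size rests on an assumed gap.** This stands. At 0.5 SD the effect is negligible. Smokers, people on drug treatment, those with systemic disease and those with severe hyposalivation are excluded, and Ds mixes three kinds of oral disease; both could keep the gap small.

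4. **Other tools are named.** STRING and Ingenuity are given for network and pathway analysis of the proteomics. They are not offered as a test of association between saliva measures and the microbiome.

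5. **A reader might infer that the intervals are too narrow because two samples per subject are treated as independent, or that arm is ignored.** The protocol does not support either. Saliva is measured at baseline and after 7 days, but nothing says the two sets of rows are stacked. The wording reads naturally as separate coefficients by time point and by arm. Each subject then counts once and arm is handled.

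**Conclusion.** The point holds for disease group only. A plain Spearman coefficient pooled over Cs and Ds can report a saliva-microbiome association when there is none inside either group. Its size runs from trivial (rho about 0.05, 6% of intervals excluding zero at a 0.5 SD gap) to serious (about 0.18 and 26% at 1 SD; 0.34 and 77% at 1.5 SD). These figures assume zero within-group correlation, normally distributed values with equal spread, and the same gap on both variables. The protocol supplies none of these.

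It would go too far to conclude that the trial's treatment result is compromised. The primary outcome is the treatment-related change in saliva parameters, analysed by ANCOVA, and the correlations do not enter it. This is a cheap improvement to a non-primary analysis that serves a stated aim.

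**What to change.** In the Statistical analysis section:
- At each time point, with one observation per subject, report Spearman coefficients with 95% intervals separately for Cs and Ds, or give a partial rank correlation adjusted for group. Any coefficient pooled over both groups is shown alongside as descriptive.
- For the treatment question, correlate within-subject changes (after 7 days minus baseline), adjusted for group and arm.
- Label all these correlations exploratory.

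**Cost:** a few lines of text and code. Separate reporting widens the intervals: near rho = 0 the half-width, tanh(1.96/√(n − 3)), is about 0.25 for n = 60, 0.31 for the 40 Ds and 0.44 for the 20 Cs. The partial version avoids most of this and loses one or two degrees of freedom. The Discussion says the study has not started, so the change can be made before any data exist.

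### The primary outcome is a change in any of several salivary parameters at P < .05, so the primary claim as defined would not be tested at the 5% type I error used for planning

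*Protocol article*

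**What the plan says.** Section 3.5 (Statistical analysis) of the protocol article defines the primary outcome as follows: "The primary outcome variable is the treatment-related change in any of the Sal parameter understudy, before and after active/placebo treatment in Cs/Ds subjects". Section 2 (Aim of the study) lists what belongs to Sal. Item (a) is "unstimulated and stimulated (paraffin-activated) salivary flow rates and pH", which makes four measures. Item (b) is "quantitative proteomics (QP), on selected targets, representing the main proteins/components of OM", with no number of targets given.

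Section 3.5 compares treatment-related changes by ANCOVA with treatment and baseline terms. On error rates it says: "The size of the sample and the power will be calculated expecting a type I error rate of 5% or less". It then states that, where appropriate, a P value below .05 "will be considered significant". No other threshold appears. The article does not rank the parameters, does not require all of them to succeed, and does not say whether controls (Cs) and diseased subjects (Ds) are pooled or tested separately for the primary outcome.

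**The concern.** A primary outcome spread over several parameters offers several chances of a significant primary result. If each parameter is tested at .05, a product no different from placebo has more than a 5% chance of yielding at least one. A sample size planned at 5% describes the trial only if the primary claim is tested at 5%.

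The trial is randomised, double-blind and placebo-controlled, and the Introduction says it tests the safety and efficacy of a marketed device. With the primary variable left open, a reader of the results could not tell a planned finding from one selected among several after the data were seen.

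**Working it through.** **Inputs from the protocol article**
- Flow and pH measures: 4 (section 2, item a).
- Proteomic targets: number not given (section 2, item b).
- Per-test threshold: .05, no adjustment stated (section 3.5).
- Subjects: 40 Ds and 20 Cs (section 3.1). Placebo goes to 20, namely 10 Cs and 10 Ds (section 3.3). Active is therefore 60 − 20 = 40, made up of 30 Ds and 10 Cs.

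**Assumptions, not in the article**
- Two-sided tests.
- Equal correlation r between the four changes, varied from 0 to 0.9.

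**Step 1. The plan's own figure.** With one test at .05, the type I error is 1 − 0.95^1 = 5.0%. The planning figure is reproduced only if the primary claim is a single test.

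**Step 2. Four measures, one pooled contrast, independent.** 1 − 0.95^4 = 1 − 0.8145 = 18.5%.

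**Step 3. Allowing for correlation.** Four two-sample t tests were simulated under no effect, 40 versus 20, with 40,000 replicates. At r = 0 the simulation gave 18.7%, which agrees with step 2 within simulation error. The last column applies if Cs (10 versus 10) and Ds (30 versus 10) are tested separately. It combines the two independent strata as 1 − (1 − p_Cs)(1 − p_Ds).

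| Correlation r | 4 tests, pooled | 8 tests, Cs and Ds separate |
|---|---|---|
| 0 (exact) | 18.5% | 1 − 0.95^8 = 33.7% |
| 0.3 | 17.4% | 31.5% |
| 0.5 | 15.8% | 28.9% |
| 0.7 | 13.0% | 24.9% |
| 0.9 | 9.5% | 18.0% |

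**Step 4. If protein targets count.** The number is unknown, so these are illustrations for independent tests. One target added to the four gives 1 − 0.95^5 = 22.6%. Sixteen targets added give 1 − 0.95^20 = 64.2%.

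**Step 5. What the remedies achieve.** One named variable with one contrast at .05 gives 5.0%. Bonferroni over four measures uses .05/4 = .0125 each and gives 1 − 0.9875^4 = 4.9% if independent, and never more than 5%. Holm gives the same guarantee and is at least as powerful.

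**Step 6. Power cost of four co-primary measures.** The standardised difference detectable with 80% power is (z for alpha/2 + z for power) × √(1/40 + 1/20), by normal approximation with no gain from baseline adjustment.
- At .05: (1.960 + 0.842) × 0.2739 = 0.77 SD.
- At .0125: (2.498 + 0.842) × 0.2739 = 0.91 SD.

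**The case against.** The strongest reply is that section 3.5 defines an outcome variable and states no success rule. The article's English is loose, and *any* may mean *each*. A reader might infer a written rule that a change in any one parameter counts as success. The text does not go that far. The arithmetic does not depend on it, though: several primary parameters, each tested at .05 with no joint-success requirement, give the same inflation under either meaning.

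Second, the 5% is worded as an input to the sample size and power calculation, and the P < .05 threshold is qualified as applying where appropriate. A reader might infer that section 3.5 contradicts itself. That is too strong, because no family-wise guarantee is given that could be contradicted. What remains is a mismatch between the planning level and the level at which the primary claim would be tested.

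Third, a multiplicity correction is often left to a statistical analysis plan, and one applied to the four measures would be compatible with this text. The lack of a correction is therefore not the finding by itself. The open primary outcome is written into the article.

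Fourth, a reader might infer that a false-positive primary result is close to certain once proteins count. That needs a large panel. The article speaks only of selected targets, gives no number, and ties proteomics to mechanism of action. The separate Cs and Ds figures are likewise conditional, since pooling is equally open.

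**Conclusion.** The concern holds in a limited form. Section 3.5 fixes the primary outcome as a change in any of at least four measures, with P < .05 as the only threshold. On the most lenient count (four flow and pH measures, Cs and Ds pooled, no proteins) the chance of at least one false-positive primary result is about 9.5% to 18.5% for assumed correlations from 0.9 down to 0. That is roughly two to four times the planning figure of 5%. If Cs and Ds are meant to be tested separately, the range is about 18% to 34%. Protein targets would raise it further, by an amount that the article does not allow one to fix.

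The figures rest on unadjusted tests at .05 and on assumed correlations. The direction does not: short of perfect correlation, more than one such test exceeds 5%.

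**What to change.** The Discussion says that the study has not started, so section 3.5 can be changed before enrolment.

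- **Preferred:** name one primary variable, compared active versus placebo by the stated ANCOVA at two-sided 5%, and make the other flow and pH measures secondary. The choice is the sponsor's. A salivary flow rate is one candidate, since section 3.1 rests the sample size on a preliminary salivary flow test, though it does not say whether that flow was unstimulated or stimulated.
- **Alternative:** keep all four flow and pH measures as co-primary, with Holm correction.
- **Either way:** state whether the primary contrast pools Cs and Ds, and declare proteomics exploratory with false discovery rate control.

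Under the preferred option, an isolated significant result on a secondary measure can no longer be called a primary success. Under the co-primary option there is also a loss of power: at the strictest Holm step (.0125, 40 versus 20), the difference detectable with 80% power rises from about 0.77 to 0.91 SD.
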